### Randomisation

After written consent has been obtained, participants and MBU staff are asked to complete the first battery of outcome measures (i.e. the baseline assessment) before participants are randomly allocated to either TAU or TAU plus Baby Triple P. Randomisation is provided by an independent CTU with an allocation ratio of 1:1 and randomised permuted blocks of size 4 and 6, and is stratified by MBU site. Once the Manchester CTU informs the project manager of the arm to which the participant has been allocated, participants are informed of the randomisation outcome and provided with a randomisation leaflet outlining what they can now expect.

### Blinding

Procedures for maintaining blindness have been developed for this trial to minimise the risk of the research assistant becoming unblinded to treatment allocation. Participants are reminded before and at the beginning of follow-up assessments not to reveal their treatment allocation to the research assistant. The trial project manager, not blinded to treatment, manages all follow-up assessments (including a telephone call to participants before the research assistant contacts participants to arrange follow-up assessments to check continued consent and remind participants not to reveal their treatment allocation to the research assistant) and monitors breaches to blindness. The research assistant is asked to indicate at the beginning of each follow-up assessment which treatment arm they think participants have been allocated to and give a confidence rating and reason for this judgement; this information is recorded in the Case Report Forms and monitored. When breaches occur prior to follow-up appointments, an alternative blinded research assistant will undertake subsequent data collection.

### Intervention and its delivery

The Baby Triple P Positive Parenting Programme consists of eight sessions (estimated to be delivered over 8–10 weeks) by trained facilitators. All participants allocated to receive this intervention will be given the Baby Triple P workbook to keep and share with their partner and family.

The first four sessions are usually delivered face-to-face on an individual basis by drawing on the information provided as presentation slides or in the handbook. These sessions are designed to enhance the knowledge, skills and confidence of parents in parenting and coping. Sessions cover advice on parenting, bonding and mother–infant interaction and relationship, partner and family support, and brief psychological coping strategies. The subsequent four sessions are designed to be delivered over the telephone, which is suitable for an inpatient setting when participants may be discharged or on home leave from the unit in preparation for discharge; they can also be delivered face-to-face. These sessions allow the participant to review progress and practice skills, thereby enhancing her parenting confidence, competence and overall wellbeing.

The intervention has a flexible delivery format, which is suitable for mothers with severe mental health. Sessions can be delivered flexibly to allow participants to attend to their baby’s needs, if required, or to pace the sessions in line with their own mental health needs. Session length can range from 45 to 90 min for the initial four sessions and 30–60 min for the telephone sessions. The content of one Baby Triple P session can also be covered in two briefer sessions and breaks can be taken.

### Intervention fidelity

Two therapists (an occupational therapist and a clinical psychologist), one from each MBU, have been trained by an accredited and experienced Baby Triple P trainer to deliver the intervention. Both therapists will work to the established Baby Triple P protocol and manual and record any deviations. Existing Baby Triple P fidelity measures [44] will be completed to assess treatment fidelity. Some sessions (approximately 5–10%) will be digitally recorded (where feasible) with participant consent and subjected to independent therapy fidelity checking by listening to the recordings to ensure the Baby Triple P protocol is being adhered to. During the intervention phase, both therapists will use the Triple P model of peer supervision [52].

### Treatment as usual (TAU)

As it is anticipated that TAU will vary based on patient need, ward acuity and staff preferences [21, 53], TAU offered to MBU patients over the study duration will be recorded. In line with all standard and individually prescribed clinical interventions as directed by the MBU clinical teams, TAU usually consists of case management using a care programme approach from their allocated MBU psychiatric nurse, pharmacological interventions from psychiatry and non-parenting, psychological interventions (e.g. cognitive behavioural therapy for depression). Nursery nurses and MBU staff also offer psychosocial interventions (e.g. Baby Massage or Video Interactive Guidance) to inpatients, which participants can choose to engage in, but these are not structured, manualised activities that focus on improving parenting competence [18, 21]. TAU will vary depending on patient needs, capacity and preferences [21]. Following MBU discharge, TAU will typically include multidisciplinary team management offered by (perinatal) community mental health teams or crisis or home treatment teams.

Participants allocated to TAU will be offered the Baby Triple P Workbook upon completion of the study (i.e. at the 6-month follow-up assessment).

### Outcomes and measures

Outcomes relate to uptake (the proportion of eligible participants consenting to partake), attrition and retention rates. Through semi-structured interviews with participants and MBU staff we will also further explore the acceptability of the study procedures and intervention. We will assess the feasibility and acceptability outcomes as follows:Feasibility of recruitment will be measured through recording how participants found out about the study, recruitment rates, number of potential participants found eligible, initially approached by MBU staff, consented to be approached by the research team, and approached about the study by the research team, reasons for declining to be approached or take part in the study if known, and percentage of eligible participants consented and their characteristics.Feasibility of randomisation will be assessed by recording number of refusals to be randomised.Engagement/retention in the study and to study procedures will be measured by recording the number of participants who withdraw and the time point at which they withdraw from the study. Reasons for leaving the study early will be recorded if known. The number of participants who complete outcome measures at each of the time points and the completeness of their data will be recorded.Engagement/retention in the intervention will be measured by recording the percentage of intervention sessions delivered, duration and maternal self-reports of time spent between sessions on Baby Triple P as well as maternal use of the workbooks. Reasons for leaving the intervention early will be recorded if known.Acceptability of the intervention and study design and procedures will be assessed post-intervention via a questionnaire (for acceptability of the intervention only) and semi-structured interviews with participants allocated to receive Baby Triple P plus TAU (*n* < 15) and MBU staff (*n* ≥ 15).

Self-report and observer-rated measures will be used alongside routinely collected information such as psychiatric history. Participants will be asked to complete an adapted version of the Family Background Questionnaire [54] asking about family sociodemographic information, family composition and maternal social support, past psychiatric and admission history, symptom presentation, diagnosis and pregnancy experiences. Data on medication type and use will be collected alongside baby care information from nursery nurses’ and clinical case-notes. Social services involvement and safeguarding information will also be collected. We will record this if it is the participant’s first admission.

Baseline assessments will be conducted prior to the start of the Baby Triple P plus TAU or TAU phase by a researcher face-to-face with participants at the MBU (referred to as Time 1). Post-intervention assessments will be conducted after the intervention phase (which will be 10 weeks (plus or minus a week) post-baseline assessments; Time 2) and at a final follow-up assessment at 6 months (26 weeks plus or minus a week, post-baseline assessments; Time 3). They will be conducted by a researcher in person at a location convenient for participants (e.g. at home or intervention setting) or at the MBU (if the participant has not been discharged) and/or over the telephone and/or via post. A flexible assessment method was chosen deliberately in order to be responsive to the needs of this population and their preferences.

Participants will be asked to complete the following self-report measures at all assessment time-points (all measures will be presented to participants in a booklet (for ease of completion) and hence the order of the questionnaire presentation will be the same for all assessments and for both MBUs):The Maternal Efficacy Questionnaire (MEQ) [55] to assess maternal confidence and competence as an indicator of overall wellbeing. Participants are asked to rate 10 questions on a 4-point Likert scale and to consider how they rate themselves in comparison to other mothers. The MEQ is a domain-specific measure of parental self-efficacy because nine of the 10 items address a mother’s self-efficacy in specific parenting tasks (e.g. soothing the baby; feeding, changing, and bathing the baby) and one item assesses general parental self-efficacy. The scale has good internal reliability (Cronbach’s alpha = 0.86) and is strongly correlated with the PSI Sense of Competence Scale (*r* = − 0.75, *p* < 0.001).The Brief Depression, Anxiety and Stress Scale (DASS) [56, 57] to assess mood. Participants rate 21 statements on a 4-point Likert Scale (ranging from 0 to 3). Internal consistencies (coefficient alpha) for each scale for the DASS normative sample were determined as Depression 0.91, Anxiety 0.84, Stress 0.90 [56]. The DASS-21 has good internal reliability with Cronbach’s alphas of 0.88 (95% confidence interval (CI) ¼ 0.87–0.89) for the Depression subscale, 0.82 (95% CI ¼ 0.80–0.83) for the Anxiety subscale, 0.90 (95% CI ¼ 0.89–0.91) for the Stress subscale, and 0.93 (95% CI ¼ 0.93–0.94) for the Total scale [57].The Postpartum Bonding Questionnaire (PBQ) [58] to assess the mother–infant relationship. Participants rate 25 statements on a 6-point Likert scale, which can be broken down into four subscales (indicating (1) general emotional bond and response to the baby, (2) feelings of anger and rejection, (3) confidence in caring for the baby and (4) possible risk to the baby). Low scores indicate good overall bonding. Its test-retest reliabilities (Pearson’s r) were of 0.95, 0.95, 0.93 and 0.77, respectively, in a sample of 30 mothers. PBQ has acceptable internal reliabilities with Cronbach’s alphas of 0.79 for impaired bonding, 0.63 for rejection and anger, and 0.63 for anxiety about care. Due to zero variance in the two items of the risk of abuse scale, the internal consistency of risk of abuse could not be determined. When these items were omitted from the total PBQ scale, Cronbach’s alpha was 0.77 [59].The Brief Symptom Inventory [60] to assess symptom severity and distress. This 53-item inventory asks participants to rate the extent to which they have been bothered (0 = not at all to 4 = extremely) in the past week by various symptoms. The Brief Symptom Inventory has nine subscales designed to assess individual symptom groups and three global indices (such as the Global Severity Index, the Positive Symptom Distress Index and the Positive Symptom Total Scale). Good internal consistencies (Cronbach’s alphas) for subscales were reported as between 0.71 (psychoticism) and 0.85 (depression) in a sample of 719 psychiatric patients. Good test-retest reliability scores (Pearson r) were reported for the Global Severity Index (*r* = 0.90), the Positive Symptom Distress Index (*r* = 0.87) and the Positive Symptoms Total Scale (*r* = 0.80) [61].The EQ-5D-5 L [62] to measure health status (in the domains of mobility, self-care, usual activity, pain/distress, and anxiety and depression). Quality-adjusted life years will be estimated from the EQ-5D as recommended by NICE for the economic evaluation of healthcare interventions [63].A bespoke health and social care resource use questionnaire to capture services used during the study, particularly following MBU discharge. It takes 5–10 min to complete. At 10 weeks post-baseline, participants will be asked to report on health and social services they have accessed since entering the study. At 6 months post-baseline, they will be asked to report on the health and social services they have accessed since the 10 weeks post-baseline assessment.

The following measures will be completed by MBU staff, if feasible, at assessment time-points or weekly if this is MBU routine practice:The Health of the Nation Outcome Scales [64] will be used to assess health outcomes. Clinical staff rate service users’ difficulties in 12 areas using a 4-point Likert scale (from ‘not a problem’ to being ‘a severe problem’). They are designed for repeated use to capture changes in a wide range of health and social domains, including psychiatric symptoms, physical health, functioning, relationships and housing. The areas are (1) overactive, aggressive, disruptive or agitated behaviour, (2) non-accidental self-injury, (3) problem drinking or drug-taking, (4) cognitive problems, (5) physical illness or disability problems, (6) problems associated with hallucinations and delusions, (7) problems with depressed mood, (8) other mental, behavioural social problems, (9) problems with relationships, (10) problems with activities of daily living, (11) problems with living conditions and (12) problems with occupation and activity.The Clinical Global Improvement Scale (CGI) [65] will be used to gauge improvements from admission to discharge. The CGI is a commonly used measure of symptom severity, treatment response and the efficacy of treatments in treatment studies of patients with mental health difficulties. The severity scale (CGI-S) is a 7-point scale that requires the clinician to rate the severity of the patient’s illness at the time of assessment, relative to the clinician’s past experience with patients who have the same diagnosis. Scores range from ‘not at all ill’ to ‘extremely ill’. The Improvement scale (CGI-I) is a 7-point scale that requires the rater to assess how much the patient’s illness has improved or worsened relative to a baseline state at the beginning of the intervention. Ratings range from ‘very much improved’ to ‘very much worse’. The CGI Efficacy Index is a 4-point × 4-point rating scale that assesses the therapeutic effect of the treatment ranging from ‘unchanged to worse’ to ‘do not significantly interfere with patient’s functioning’.The Brief Psychiatric Rating Scale [66] is a scale which a clinician or researcher may use to measure 24 symptoms, including depression, anxiety, hallucinations and unusual behaviours. Each symptom is rated on a 7-point Likert scale (from not present to extremely severe); it is commonly used in psychiatric settings.The Louis MACRO (Mother and Child Risk Observation) Measure [67] will be used to assess infant wellbeing and the mother–infant relationship. Using a 5-point Likert scale, MBU staff rate mothers on 10 items across five domains (including safety, care, emotional responsiveness, mother’s mental stage and infant characteristics that may contribute to parenting difficulties). The Louis MACRO has excellent internal reliability with Cronbach’s alphas of 0.96 for the total scale and between 0.79 and 0.95 for the 10-item subscales. Its subscales’ inter-rater reliabilities (Pearson’s r) were between 0.81 and 0.93 and its test-retest reliability scores were 0.71 to 0.93. Note that this measure is routinely used by some MBUs.

### Assessment of acceptability of intervention and study procedures

Acceptability will be examined quantitatively through study uptake, attrition and retention rates as well qualitatively through interviews because participants’ experiences of participation in a trial and its procedures (e.g. quantity and frequency of assessments, randomisation process) are important for informing the design and methods of a future full-scale RCT. In addition, the acceptability of the intervention will be assessed through a validated satisfaction questionnaire [68] and through qualitative research interviews (described below) in order to examine if the current intervention is considered to be acceptable and appropriate for this population.

The Client Satisfaction Questionnaire [68] will be used to collect information on participants’ views on the acceptability of Baby Triple P and their overall satisfaction with this intervention. Participants are asked to rate 13 questions (e.g. to what extent has the programme met your needs?) on a 7-point Likert scale and provide answers to three open-ended questions (e.g. do you have any other comments about this programme?). This will be administered to participants (allocated to receive Baby Triple P plus TAU) in person or over the telephone or via post after they have completed the intervention.

Semi-structured individual interviews will be conducted post-intervention with MBU staff and trial participants allocated to the intervention arm prior to or around the time of their final follow-up assessment. All participants will be given a separate participant information sheet and consent form. Staff participants will be recruited through an advert or poster displayed on the ward. All interviewees will be interviewed at a time and place convenient to them or via telephone for up to 90 min. Interviewees will be given the choice to be interviewed by a researcher who works on the study at the same MBU they were admitted to and who they know or by a researcher who works at a different MBU and who they do not know. This is to ensure that participants feel comfortable expressing their views in the interview.

Interviews with participants and MBU staff will explore (1) acceptability, usefulness and user-friendliness of the intervention, (2) changes in and any benefits to themselves since receiving the intervention, (3) perceived changes/improvements to the intervention needed, (4) ways to increase adherence to and engagement in the intervention, (5) views on the procedures of the trial, and (6) perceived changes/improvements needed to increase adherence to and engagement in the study.

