**Fig. 2 Fig2:**
[figure not shown]
Schedule of enrolment, interventions and assessments

Assuming a drop-out rate of 10% between recruitment and randomisation in an inpatient setting, a maximum of 66 participants will be recruited and a maximum of 60 will be randomised after completion of baseline measures during their inpatient admission to a MBU. Participants will be randomly allocated, using an independent Clinical Trials Unit (CTU), to TAU or to TAU plus eight sessions of Baby Triple P. Additional sessions can be offered, for example, to conduct an initial assessment and, if required, the intervention can be delivered more flexibly.

Participants are followed up at 10 weeks post-baseline and at 6 months post-baseline. The end of treatment is not fixed but dependent on progress and participants’ capacity to engage, whereas assessment time points are fixed.

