### Nested process evaluation: inclusion and exclusion criteria for participants and staff

As part of a nested process evaluation, we will undertake a qualitative study of staff and patient experiences and views of Baby Triple P and a sample of participants (*n* < 15 women and *n* ≥ 15 MBU staff) will be interviewed. Interviews will explore participants’ and MBU staff experiences and expectations of the study procedures and the intervention alongside its content. Facilitators and barriers to implementation of this type of intervention within a MBU setting will be identified.

Participants (*n* < 15) who were allocated to the intervention arm plus TAU, irrespective of subsequent intervention engagement, will be asked to take part in interviews for the nested qualitative aspect of this study. The same inclusion and exclusion criteria as above will apply.

MBU staff participants (*n* ≥ 15) will also be recruited if they are permanent full-time or part-time members of the MBU staff team and have worked on the MBU for at least 6 months. Psychiatry and medical MBU staff will also be recruited if they have worked on the MBU for at least 4 months. Separate participant information sheets and consent forms for this aspect of the study will be used; similar consent procedures outlined below will apply.

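### The satisfaction questionnaire is timed to completion of Baby Triple P, with no stated provision for women who stop early, so its scores probably overstate satisfaction

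*Protocol article*

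**What the plan says.** Under Assessment of acceptability of intervention and study procedures, the recipients of the questionnaire are named by arm: "This will be administered to participants (allocated to receive Baby Triple P plus TAU"). The timing follows in the same sentence: "in person or over the telephone or via post after they have completed the intervention". The form has 13 items on a 7-point scale ("Participants are asked to rate 13 questions") and three open questions.

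Outcomes and measures describes the same instrument more loosely: intervention acceptability "will be assessed post-intervention via a questionnaire (for acceptability of the intervention only"). It carries no completion condition there.

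Other parts of the article bear on women who stop:

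- Outcomes and measures expects some to do so: "Reasons for leaving the intervention early will be recorded if known".
- The nested process evaluation section reaches them explicitly. Women in the intervention arm, "irrespective of subsequent intervention engagement, will be asked to take part in interviews", with fewer than 15 to be interviewed.
- The acceptability section also uses rates: "Acceptability will be examined quantitatively through study uptake, attrition and retention rates".
- Trial design, in the text after Figure 2, leaves the end of the programme open: "The end of treatment is not fixed but dependent on progress" and on the woman's capacity to engage.

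**The concern.** Whether the programme is acceptable to mothers is a stated objective, and the findings are meant to refine the programme and inform a larger trial. A satisfaction score collected only from women who finish is conditioned on an outcome that is itself related to satisfaction: a woman who dislikes the sessions is more likely to stop, and once she stops she no longer has a completion date at which to be asked.

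This is a rule of data collection, so the analysis cannot put it right later. Scores that were never requested cannot be recovered. A reader of the results would then see a rating that appears to speak for the women offered the programme but speaks only for those who stayed with it.

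**Working it through.** **Wording compared.**

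| Source in the article | Who | When |
|---|---|---|
| Acceptability section, questionnaire | Women allocated to Baby Triple P | After completing the intervention |
| Outcomes and measures, questionnaire | Not restricted | Post-intervention |
| Nested process evaluation, interviews | Women allocated to Baby Triple P, whatever their engagement | Post-intervention, before or around the final follow-up (timing from the acceptability section) |

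The interviews have an explicit clause that brings in women who disengage. The questionnaire has none, and in its fuller description it carries a completion condition. The looser term does not settle the matter. Outcomes and measures places its post-intervention assessments at 10 weeks (plus or minus one) after baseline, whereas completion varies from woman to woman and may never occur.

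**Size.** The article states no expected completion rate and no expected score, so there is no figure of its own to reproduce. The size can only be shown under assumptions.

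Inputs:

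- Allocated to Baby Triple P: at most 60 randomised at 1:1, so about 30 (Trial design; Randomisation).
- Item scale: 7 points, 13 items (acceptability section).
- Share completing, c: assumed 50% to 90%.
- Gap per item between the completers' mean and the mean that non-completers would have given, d: assumed 1 to 2 points.

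Formulas: women without a score = 30 × (1 − c); overstatement of the mean = (1 − c) × d.

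| c | Without a score | d = 1 | d = 2 |
|---|---|---|---|
| 90% | 3 | 0.10 | 0.20 |
| 80% | 6 | 0.20 | 0.40 |
| 70% | 9 | 0.30 | 0.60 |
| 60% | 12 | 0.40 | 0.80 |
| 50% | 15 | 0.50 | 1.00 |

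Worked example at 70% completion, with completers averaging 6 and non-completers 4: (21 × 6 + 9 × 4) / 30 = 162 / 30 = 5.4. The completer-only mean of 6.0 is therefore 0.6 too high.

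On a 13-item total, the range 0.10 to 1.00 per item becomes 13 × 0.10 = 1.3 to 13 × 1.00 = 13.0 points. If c = 100% or d = 0, the overstatement is zero.

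**The case against.** The best case for the plan has four parts.

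1. **The clause may be about timing only.** Recipients are defined by allocation, the outcomes section says only post-intervention, and the end of treatment depends on progress and capacity to engage. A woman who stops after three sessions could be regarded as having reached her own end of treatment. This reading is possible and means the wording is ambiguous. It does not remove the problem, because nothing tells a site to send the form to a woman who stops, and the interview clause shows that the authors wrote such an instruction where they wanted one.

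2. **Acceptability does not rest on this score.** This stands. A reader might infer that the questionnaire is the only quantitative evidence on acceptability, or that women who disliked the programme drop out of the acceptability assessment altogether. The documents support neither. Uptake, attrition and retention are named as quantitative indicators; sessions delivered, time spent between sessions and workbook use are recorded; interviews are open whatever the engagement; and reasons for leaving are noted where known. A high score from few completers would also appear beside the CONSORT participant flow and the tabulated feasibility findings. However, fewer than 15 interviews, together with reasons recorded only if known, do not replace the missing ratings.

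3. **No decision hangs on the score.** The article sets no satisfaction threshold, and no comparison between arms uses it. This also stands, and it limits the consequence.

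4. **Completion may be high.** All 12 women who received Baby Triple P in the earlier pilot completed every session. With that completion the bias would be nil. But that pilot enrolled mothers with postnatal depression, and the present article itself treats engagement and attrition on a Mother and Baby Unit as open questions.

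**Conclusion.** The point holds in a limited form. The one scored rating of Baby Triple P by its recipients is tied to completion, without provision for women who stop early. Followed literally, it yields a completers-only score.

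Upward bias is the likely direction, not a certainty. Its size is not derivable from the article: 0.1 to 1.0 points per 7-point item rests wholly on the assumed 50% to 90% completion and a 1 to 2 point gap. With about 30 women allocated, 3 to 15 would have no score under the same completion range.

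The affected quantity is a descriptive satisfaction score. The wider acceptability assessment still reaches early leavers by other routes, and the document does not show that a decision on a later trial would be wrong because of this. It is nevertheless worth correcting, because it is cheap to fix before the data are collected and cannot be repaired afterwards.

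**What to change.** State in both Outcomes and measures and the acceptability section that every woman allocated to Baby Triple P who received at least one session is offered the questionnaire when she finishes or stops the intervention, regardless of how many sessions she had. Set a latest date: the 10-week assessment, or the 6-month assessment if her sessions are still continuing at 10 weeks.

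Report the scores by number of sessions received, with the number responding out of all allocated and the number who had no sessions. A single mean over everyone allocated at a fixed 10 weeks would not be a good substitute. Delivery is estimated at 8 to 10 weeks and is flexible, so some women would be mid-programme, and women with no sessions have nothing to rate.

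The article does not say who hands out the form. As only one arm receives it, the unblinded project manager could handle it if it falls near a follow-up visit.

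The cost is a sentence in each section and a few more questionnaires in person, by telephone or by post. Some respondents will have seen only part of the programme, which is why the scores should be shown by sessions received. Non-response among early leavers will remain, but it will be counted.
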